### Participants

#### Adolescents and Their Parents

All adolescents in our study will be boys, as girls are not referred to the two JJIs concerned. The boys will be between 12 and 18 years old at the time of placement. All youth placed in a FC group will be offered FC, but not all of them will be included in our study. An adolescent will be excluded (1) if his stay in the short-term stay group lasts less than 14 days (we need a minimum of two weeks to complete all assessments for the study); (2) if he does not have a parent or a parent figure; (3) if he already participated in our study during a previous stay; (4) if he does not understand Dutch; (5) if he and his parents refuse to take part in the assessments; (6) if he is already sentenced by the juvenile judge to a so-called PIJ order (Placement in an Institution for Juveniles for mandatory treatment) which implies long-term detention with treatment, or (7) if he is temporarily transferred from another institution.

As our assessments will be part of the Routine Outcome Monitoring (ROM) and of the standard screening and diagnostic procedures, psychologists can withhold the adolescent or his family from assessments, for example in case of severe psychiatric disorders. Reasons for excluding participants from the study will be noted. Consequently, we will first consult psychologists before approaching adolescents and their parents for the interviews. In general, following the psychologists’ advice, we will not approach them in case of an alleged sex crime or when severe psychiatric disorders such as mental retardation, psychosis, autism, or acute suicidal behaviors are present.

Because the questionnaires in the quantitative part of our study are embedded in the standard procedures in the institutions, no incentives will be used for youth and parents. For the interviews, however, youths will receive extra television time in their rooms and parents will receive a small incentive such as a mug filled with chocolates and a personal thank you note.

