### Recruitment and Sample Size

Adolescents and parents are informed of the JJI’s research activities by a flyer in the information leaflets from the JJI. The flyer informs that the data will be used anonymously in research studies and that parents can address their questions concerning these activities to their child’s mentor (one of the group workers) or to the psychologist.

The JJIs in the Netherlands jointly apply ROM and standard screening and diagnostic procedures for detained adolescents and their parents. As our assessments will be embedded in these procedures, the quantitative part of our study will use data collected in the two participating JJIs by these means. Recruitment of adolescents and their parents in the quantitative part of our study will last 21 months, including the pilot stage of 7 months. Based on records from 2011, the year prior to the pilot stage, we estimate that in 21 months, 300 adolescents will be placed in the groups concerned. Taking into account the exclusion criteria, we expect to recruit 160 adolescents and parents for the present study. Based on previous research, this number suffices for establishing statistically significant differences on quantitative measures between the two conditions [9].

As for qualitative studies, 10 interviews are generally sufficient to achieve saturation (ie, the point where additional interviews do not yield new essential information regarding the research question) [32]. Once an eligible adolescent is placed in a short-term stay group (either FC or UC), he and his parents will be invited to participate in the qualitative part of the study. If they are willing to participate, an appointment will be made for the interview. We will interview 10 boys (5 aged < 16 years and 5 aged > 16 years) in each JJI (N=20). We will also interview 20 parents (10 in in each JJI, 10 fathers and 10 mothers, 10 with a detained child aged < 16 years, and 10 with a detained child aged > 16 years). Finally, we will interview 20 FC group workers and 20 UC group workers.

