#### Demographics

Demographic data on age, place of birth, and ethnic background will be retrieved from the individual JJI database and from the joint ROM-JJI database. Because these databases do not contain information on family background, housing, past treatment, school careers, and jobs, we will use a short questionnaire to gather these data.

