#### JJI Staff

We devised questionnaires for JJI staff (group workers, team leaders, psychologists) about working with families and about using the family perspective in their thinking and in day-to-day interventions. The questionnaire has two parts, part A and part B. Part A contains 12 items to be rated on a five-point scale and includes questions such as “Do you invite parents of every mentor-child for a meeting?”, “Do you invite parents of every mentor-child for a tour through the facility?”, “Do you inform parents on the same day when their child was involved in an incident?”, and “If parents are divorced, do you involve both parents in the same way?”. Part B contains 17 items to be rated on a scale of 1-10. This part includes questions such as “How satisfied are you with the course of the contact with the parents?”, “How satisfied are you with the way in which you involve parents during their son’s stay?”, and it includes statements such as “Parents are difficult to work with”, “Parents are indispensable for reducing recidivism”, and “Parents are a source of support for staff”.

These questionnaires will be filled out every three months. On an additional form, psychologists will note where the adolescent is going to live after leaving the short-term stay group.

To assess if staff members adhere to the guidelines of the FC program, they will use logbooks and will fill out short forms on family-centered activities undertaken. This will enable us to assess program integrity. The overviews of these logs are shared during team meetings and with the managements, enabling managers and team leaders to monitor and direct the organization of family-centered activities.

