### Analyses

#### Quantitative Analyses

All statistical analyses will be performed using SPSS 23. In a future paper, we will provide a flowchart of participants in our study, including reasons for exclusion. Descriptive statistics will be presented as means and standard deviations for all continuous variables and subscales. Additionally, frequency distributions or qualitative descriptions of all categorical variables will be presented for each group. The groups will be defined as FC or UC. We will test if these groups differ on demographic factors. If these differences exist, we will use these factors as covariates in our analyses. If necessary, we will also include the JJI in which an adolescent is placed as a covariate. We will perform within-group pre-post comparisons, between-group comparisons (FC vs UC), and repeated measures analyses. The selection of a specific test will depend on which hypothesis is tested and on the characteristics of the corresponding data (eg, categorical, ordinal, or interval level and normally or non-normally distributed). Table 3 shows the planned analyses to test our hypotheses for comparing FC with UC in case of normally distributed data. For combining the within-group pre-post comparisons and the between-group comparisons in our analyses, we will use the repeated measures ANOVA. Because the normality of the distribution of the data cannot be determined beforehand, the final analyses will be selected after the data is gathered. In analyzing the hypotheses, two-tailed analyses will be performed and we will correct for multiple testing.

**Table 3 table3:** Planned analysis for between-group hypotheses.

Hypothesis	Data source	Analysis
FC increases parents’ involvement with their detained child	Registration logs visits	Unpaired *t* test
FC increases the motivation of the adolescents and parents for accepting treatment and guidance by JJI staff and for taking part in family meetings	ATMQ youth total score Motivation items youth	Unpaired *t* test Pearson’s Chi-square test
	Motivation items parents	Pearson’s Chi-square test
FC adolescents show less problem behavior	Incidents in JJI Cannabis database	Unpaired *t* test Unpaired *t* test
FC improves family interactions	FES	Unpaired *t* test
FC parents experience less parenting stress	PSQ	Pearson’s Chi-square test
FC youth more often return to their families’ home upon discharge	Registrations logs living situation after discharge	Pearson’s Chi-square test

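### Hypothesis 6 speaks of a return home, but its planned test uses destination only and ignores where the boy lived before placement

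*Protocol article*

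**What the plan says.** The hypothesis, in Study Objectives and Research Questions and again in Table 3 (Quantitative Analyses), is "FC youth more often return to their families’ home upon discharge". Table 3 names one data source for it, "Registrations logs living situation after discharge", and one test, Pearson's chi-square. Under JJI Staff, the recording procedure is that "psychologists will note where the adolescent is going to live after leaving the short-term stay group".

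Three other statements bear on the point:

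- **Eligibility** (Adolescents and Their Parents). A boy is excluded "if he does not have a parent or a parent figure". Living away from the family before placement is not an exclusion.
- **Housing data** (Demographics). "Because these databases do not contain information on family background, housing, past treatment, school careers, and jobs, we will use a short questionnaire". The article does not connect this item to hypothesis 6.
- **Covariates** (Quantitative Analyses). FC and UC are tested for differences on demographic factors: "If these differences exist, we will use these factors as covariates in our analyses".

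On sample size, "we expect to recruit 160 adolescents and parents for the present study". Setting describes three FC and two UC groups, chosen by management on pragmatic grounds. Boys are placed according to free slots, without randomisation.

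**The concern.** A return has an origin and a destination, and the row for hypothesis 6 uses only the destination. A boy who goes back to residential care looks the same as a home-living boy who did not get home. A boy who moves in with his parents for the first time looks the same as one who went back to them.

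Two consequences follow if the row is applied as written:

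1. **Dilution.** If FC helps mainly boys who already lived at home, including the others in an unadjusted comparison shrinks the difference and adds variance.
2. **Confounding.** If the FC and UC groups differ in the share who lived elsewhere, that difference carries over into destination. The covariate rule is a weak protection. It acts only when a difference is detected, and a Pearson chi-square has no place for a covariate.

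**Working it through.** **The plan's own figure.** The 160 cannot be reproduced. The article supports it only with "Based on previous research, this number suffices for establishing statistically significant differences on quantitative measures between the two conditions" and gives no effect size, rates, alpha or power. It serves below only as the planned number.

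**Inputs.** From the article: N = 160, and three FC to two UC groups. With equal inflow per group (an assumption), this gives 96 FC and 64 UC. Everything else is assumed: the share q who did not live with family before placement, the rates of going to the family home, the FC effect, and a two-sided 0.05 level without multiplicity correction.

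**1. Dilution with equal q in both groups.** Assume 60% (UC) and 80% (FC) of home-living boys go home. Among the others, assume 10% in both groups, that is, no FC effect in them. Then

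difference in destination = (1 − q) × 20 points.

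Power is by normal approximation. The stratified column is the Mantel-Haenszel-type test on all boys.

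| q | UC v FC, all boys | Difference | Power, unadjusted | Power, stratified | Power, home-living boys only |
|---|---|---|---|---|---|
| 0 | 60% v 80% | 20 | 78% | 78% | 78% |
| 10% | 55% v 73% | 18 | 65% | 72% | 74% |
| 20% | 50% v 66% | 16 | 52% | 65% | 69% |
| 30% | 45% v 59% | 14 | 41% | 56% | 63% |

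Stratified entry at q = 20%. The stratum weights n1n2/(n1 + n2) are 51.2 × 76.8/128 = 30.72 (home) and 12.8 × 19.2/32 = 7.68 (elsewhere).

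- Weighted difference: 30.72 × 0.20 + 7.68 × 0 = 6.144.
- Null variance, with pooled rates 0.72 and 0.10: 30.72 × 0.72 × 0.28 + 7.68 × 0.10 × 0.90 = 6.884.
- Variance under the alternative: 30.72² × (0.24/51.2 + 0.16/76.8) + 7.68² × (0.09/12.8 + 0.09/19.2) = 7.081.
- Power: Φ[(6.144 − 1.96 × √6.884)/√7.081] = Φ(0.376) = 65%.

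Stratifying recovers much of the lost power. The average difference over all boys is still 16 points; only separate reporting shows the 20.

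**2. Spurious difference with unequal q and no true effect.** Assume 70% of home-living boys and 10% of the others go home, under both programs.

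- 25% of UC and 15% of FC boys lived elsewhere. UC: 0.75 × 0.70 + 0.25 × 0.10 = 55%. FC: 0.85 × 0.70 + 0.15 × 0.10 = 61%. The difference is 6 points and the rejection rate 11.8%.
- 30% v 10%: 52% v 64%. The difference is 12 points and the rejection rate 32.8%.
- 20% in both: no difference, and the rejection rate is 5.0%.

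**3. Would the covariate rule notice a 10-point imbalance?** SE = √[q(1 − q)(1/96 + 1/64)].

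| Pooled q | SE | z = 0.10/SE | Two-sided p |
|---|---|---|---|
| 10% | 0.048 | 2.07 | 0.04 |
| 20% | 0.065 | 1.55 | 0.12 |
| 30% | 0.074 | 1.35 | 0.18 |

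At a conventional 0.05 level the rule would act at 10% but not at 20% or 30%. The 25% v 15% case (pooled 19%, p = 0.11) would go unadjusted. The 30% v 10% case (pooled 18%, SE 0.062, p = 0.001) would be caught.

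**The case against.** The strongest reply is that the article gives no coding rule for this outcome. Table 3 lists hypotheses, data sources and tests; it does not define outcomes, and coding can properly be left to a fuller document. Nor does the article say that any included boy lived away from his family. A reader might infer that such boys are being miscounted. The text does not support that: misclassification is possible, not shown. What remains is that the named data source and test do not match the wording of the hypothesis.

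A second reply is that *return home upon discharge* can simply mean leaving the institution to live with the family. A boy who newly moves in with his parents is then a success, and a program built on involving parents may fairly claim him. This is a defensible estimand. A reader might also infer that the test must be restricted to boys who lived at home before; that does not follow, and the restriction would discard such a benefit. With balanced prior residence, the destination comparison keeps its type I error.

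Third, placement by free slots makes a strong imbalance less likely, nothing in the article points to one, and demographic differences are to be adjusted for. This stands in part. Free-slot placement does not guarantee balance, and the adjustment depends on detecting a difference and on a test that can carry it. The article does leave the final choice of analysis until the data are in, but the reason it gives is normality, which has no bearing on a categorical outcome. The limit of a chi-square without covariates is shared by other rows of Table 3. It weighs more here because prior residence is so plainly related to destination.

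**Conclusion.** The point holds as a mismatch between hypothesis and test, with a foreseeable confounder left out of a non-randomised comparison. It does not establish that the result will be wrong. All magnitudes are illustrations: the article gives no share of boys living elsewhere and no rates of going home. The dilution figures also assume that FC has no effect in boys who lived elsewhere; if FC helps them too, the dilution is smaller.

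Under those assumptions, and with 10% to 30% living elsewhere, a 20-point effect appears as 18 to 14 points. Power for the unadjusted test falls from 78% to between 65% and 41%. An undetected 10-point imbalance creates a difference of about 6 points and raises the false-positive rate from 5% to about 12%. The point touches one of eight hypotheses. It is worth correcting because the correction is cheap.

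**What to change.** 1. Keep all boys and define the outcome as discharged to the family home.
2. Replace the Pearson chi-square for hypothesis 6 with a Mantel-Haenszel test stratified by prior living situation, or a logistic model containing it, whether or not FC and UC differ on it.
3. Report the FC–UC comparison separately for boys who did and did not live with family before placement, and use the word *return* only for the former.
4. Confirm that the housing item in the short questionnaire records where the boy lived before placement. The article does not say so. If it records something else, the adjustment depends on another source, since the Discussion states that data collection ended in 2015.

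The cost is one definition and one changed test, with no new data if step 4 is confirmed. Boys with unknown prior residence need their own category or drop out of the analysis, and the separate results will be less precise than the overall one.

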### Study Objectives and Research Questions

The overall aim of our study is to evaluate FC in the first two years after the first steps of its implementation in short-term stay groups in JJIs. The key question to be answered in the quantitative part in the second stage of the study is if FC has additional value compared to UC. We will test the following hypotheses comparing FC with UC during detention: (1) FC increases parents’ involvement with their detained child; (2) FC increases the motivation of the adolescent and his parents for accepting treatment and guidance by JJI staff and for taking part in family meetings; (3) FC adolescents show less problem behavior; (4) FC improves family interactions; (5) FC parents experience less parenting stress; (6) FC youth more often return to their families’ home upon discharge; (7) FC enhances adolescents’ and parents’ satisfaction with the JJI; (8) In FC groups, JJI staff members are more satisfied, feel more confident in their contact with parents, and more often incorporate the family perspective in their thinking.

Finally, we will study if parents who participate in family-centered activities, differ from parents who do not participate based on characteristics such as proximity to the JJI, age of their child, duration of his stay, and baseline outcomes in other demographics, family functioning, parenting stress, treatment motivation, and satisfaction.

The aim of the qualitative part of the study is to trace which factors influence parental involvement. We will interview adolescents, parents, and group workers from short-term stay groups based on the following research questions: (1) How do adolescents, parents, and group workers feel about the current involvement of parents in FC and UC? (2) What are the attitudes of FC and UC group workers towards working with parents? (3) What are the needs, wishes, and expectations of adolescents, parents, and group workers concerning FC?

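### Hypothesis 6 (return to the family home) is tested without fixed adjustment for where the boy lived before detention; adjustment depends on a baseline test

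*Protocol article*

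**What the plan says.** Under Study Objectives and Research Questions, hypothesis 6 reads "FC youth more often return to their families’ home upon discharge". Table 3 (Quantitative Analyses) lists one data source for it, "Registrations logs living situation after discharge", and one test, "Pearson’s Chi-square test". The JJI Staff section explains how the outcome arises: on a separate form, "psychologists will note where the adolescent is going to live after leaving the short-term stay group". Only the destination is recorded there.

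Eligibility (Adolescents and Their Parents) excludes a boy "if he does not have a parent or a parent figure". No exclusion concerns where he was living, so boys who lived away from their family before detention can be included.

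Information on housing is collected. The Demographics section says: "Because these databases do not contain information on family background, housing, past treatment, school careers, and jobs, we will use a short questionnaire". The only route from that item into the test is the general covariate rule in Quantitative Analyses: "We will test if these groups differ on demographic factors", and then "If these differences exist, we will use these factors as covariates in our analyses". The institution (JJI) may be added as a covariate if necessary.

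**The concern.** Whether a boy goes to his family's home after detention is likely to depend heavily on whether he lived there before. The hypothesis itself implies this, because it speaks of returning. Yet prior living situation has no fixed place in the test.

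Two things are at stake.

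- **Precision.** Adjusting for a strong predictor of a binary outcome removes noise even when the arms are perfectly balanced. Under the stated rule, balance is exactly when no adjustment is made.
- **Imbalance.** Boys are not randomised. An imbalance too small to be significant would stay in the comparison and move the result of hypothesis 6 in either direction.

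Always adjusting would deal with both and, if the housing item covers residence before detention, needs no new data.

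**Working it through.** The article gives no power figure for hypothesis 6, so there is none to reproduce. What follows is an illustration.

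**Inputs.** From the article: 160 boys expected (Recruitment and Sample Size); three FC and two UC groups (Setting). If the groups fill equally, that is 160 × 3/5 = 96 FC and 64 UC. Assumed: 70% lived at home before; of these, 60% (UC) and 80% (FC) go home; of the others, 10% in both arms; two-sided 5%; boys independent.

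**Formula.** For each stratum let w = n(FC) × n(UC) / (n(FC) + n(UC)). The signal is S = Σ w × difference. The variance is V = Σ w × p(1 − p), with p the pooled rate. Power ≈ Φ(S/√V − 1.96).

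**Test as planned (one stratum).**
- Rates: UC 0.7 × 0.6 + 0.3 × 0.1 = 0.45; FC 0.7 × 0.8 + 0.3 × 0.1 = 0.59.
- w = 96 × 64/160 = 38.4; S = 38.4 × 0.14 = 5.376.
- p = (64 × 0.45 + 96 × 0.59)/160 = 0.534; V = 38.4 × 0.534 × 0.466 = 9.556.
- Power ≈ Φ(5.376/3.091 − 1.96) = Φ(−0.22) = 41%.

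**Stratified by prior living situation, all boys kept.**
- From home (67.2 FC, 44.8 UC): w = 26.88; p = 0.72; contribution to V = 26.88 × 0.72 × 0.28 = 5.419.
- From elsewhere (28.8 FC, 19.2 UC): w = 11.52; p = 0.10; contribution = 11.52 × 0.10 × 0.90 = 1.037.
- S = 26.88 × 0.20 + 11.52 × 0 = 5.376; V = 6.456.
- Power ≈ Φ(5.376/2.541 − 1.96) = Φ(0.16) = 56%.

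The signal is the same; only the variance falls, by a factor of 9.556/6.456 = 1.48. Simulation gives the same two figures to within a point, and 41% to 42% for the stated rule of testing first and adjusting if significant. With no true imbalance the baseline test triggers adjustment only about 5% of the time.

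**Range over the unknown share living at home** (same formula):

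| At home before | Planned | Adjusted |
|---|---|---|
| 60% | 32% | 47% |
| 70% | 41% | 56% |
| 80% | 52% | 65% |
| 90% | 65% | 72% |

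**If FC also helps boys from elsewhere** (70% at home; UC stays at 10%):
- FC 20%: planned S = 38.4 × 0.17 = 6.528, V = 9.496, power 56%; adjusted S = 6.528, V = 5.419 + 1.548 = 6.967, power 70%.
- FC 30%: planned S = 7.68, V = 9.412, power 71%; adjusted S = 7.68, V = 5.419 + 1.977 = 7.396, power 81%.
- A test restricted to boys from home stays at Φ(5.376/√5.419 − 1.96) = 63% or 64%, whatever happens to the others.

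**What the baseline test misses.** The standard error of the difference in prior home share is √(0.7 × 0.3 × (1/96 + 1/64)) = 7.4 points, so differences up to about 1.96 × 7.4 = 14.5 points go unflagged. If boys from home are 60 points more likely to go home (70% against 10%), a one-standard-error imbalance shifts the result by 0.6 × 7.4 = 4.4 points with no FC effect. True home shares of 75% (UC) and 85% (FC) are flagged 36% of the time; 70% and 85%, 62% of the time.

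**False positives under those two imbalances**, with no FC effect and the same 70% and 10%: about 12% and 20% with the plain chi-square, but about 6% if the covariate rule is carried out.

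**The case against.** The strongest reply is that the plan already covers this. Housing is collected as a demographic factor, and demographic factors that differ become covariates. A reader might infer that any difference in prior living situation will pass for an effect of FC. The article does not support that: if the rule is carried out, false positives stay near 6%, and the Setting section says that placement does not depend on the boys' characteristics. This stands, and it makes confounding the smaller part of the point. It does not answer the loss of precision, which is greatest when the rule is not triggered.

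A reader might also infer that boys who lived elsewhere are scored as failures to return. No section states the coding or the denominator. A boy who lived elsewhere and is discharged to his family could count as a success, and the illustration allows 10% of them to do so.

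It is tempting to conclude that the test should be limited to boys who lived at home. That would discard reunification, which FC may well promote, since it engages parents and offers family therapy that continues after discharge. The restricted test can then be the weaker one: about 63% against 71% for the planned test in the last scenario. Adjusting with all boys kept is ahead of the planned test in every scenario shown.

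Finally, Table 3 is not final, and an article may leave the model to a fuller document. But the reason given for deferring the choice is normality, which does not bear on a yes/no outcome. The point concerns the covariate rule that the article does state.

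**Conclusion.** The point holds as a cheap improvement, not as an error that invalidates hypothesis 6. The test named is unadjusted, and the rule for adding prior living situation depends on a significance test with little ability to detect moderate imbalance. Under the assumed rates, always adjusting raises power from about 41% to 56%, and by 7 to 15 points over home shares of 60% to 90%. The stated rule recovers almost none of this.

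All rates are assumptions. The article gives neither the share of boys living away from home nor how strongly prior residence predicts destination. If nearly all boys lived at home, or the link is weak, the gain is small. The plan's correction for multiple testing would lower all these powers; its method is not given. The article also does not say outright that the housing item means residence before detention.

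**What to change.** 1. Define the outcome for hypothesis 6 as discharged to the family home, yes or no, over all included boys.
2. Replace the chi-square with logistic regression of that outcome on FC versus UC, with prior living situation and JJI as fixed terms whatever any baseline test shows. A Mantel-Haenszel test stratified by the same two factors would also serve. JJI belongs there because the ratio of FC to UC groups is 2:1 in one institution and 1:1 in the other.
3. Confirm that the housing item records where the boy lived before detention, and state how missing answers are handled.
4. Report percentages by prior living situation as a supporting analysis. Do not restrict the main test to boys who lived at home.

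The cost is slightly more analysis work and no new data, provided step 3 is confirmed. The Discussion says that data collection is complete and first outcomes are being analysed, so the change should be recorded before hypothesis 6 is examined by group, or else reported as made afterwards.

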## Methods

### Design

Our study has a practice-based nature. Carrying out research in a setting such as a JJI is challenging, as it is in most practice-based studies [25]. It is virtually impossible to organize a randomized controlled trial in a JJI. First, judges are not likely to agree with randomizing adjudicated adolescents to different detention conditions. Second, JJIs struggle with relative instability of staff due to high turnover and high rates of absenteeism [26]. Another barrier for conducting research in JJIs is the unfamiliarity among most of the institution’s staff with the principles and benefits of research studies [23]. To prepare JJI personnel for implementing and evaluating FC, we trained them to internalize FC rationale and FC practice and we organized a seven-month pilot stage. In the remainder of the pilot stage, we found FC short-term stay groups to differ in number and nature of family-oriented actions, although all group workers had received the same training. Also, we noticed that not every parent visited their child or attended every kind of family activity organized by the JJI. Additionally, the preliminary analyses of the pilot data showed the surprising finding that most parents and youths report few family problems, while at the same time they report motivation for family therapy. In setting up the actual study, we used feedback from staff and the results of monitoring the groups during the pilot stage to improve the FC program.

Evaluating the pilot stage gave rise to our final study design, in which the pilot is considered as the first stage, see Figure 1.

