FC enhances adolescents’ and parents’ satisfaction with the JJI	Satisfaction questionnaire-A Satisfaction questionnaire-B	Pearson’s Chi-square test Unpaired *t* test
In FC groups, JJI staff members are more satisfied, feel more confident in their contact with parents, and more often incorporate the family perspective in thinking	Questionnaire staff-A	Generalized estimating equations
	Questionnaire staff-B	General linear model repeated measures

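### Staff questionnaire B is repeated every three months, but the planned GLM repeated measures analyses only staff with every round, in a setting with high turnover and absenteeism

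*Protocol article*

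**What the plan says.** In Table 3 (Quantitative Analyses), hypothesis 8 on staff satisfaction, confidence and family perspective is tested with two parts of one staff questionnaire. Part A gets "Generalized estimating equations"; part B gets "General linear model repeated measures". On software: "All statistical analyses will be performed using SPSS 23".

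On timing, the JJI Staff section states: "These questionnaires will be filled out every three months". It names group workers, team leaders and psychologists as respondents. No start, end or number of rounds is given.

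On staff continuity, the Design section states: "JJIs struggle with relative instability of staff due to high turnover and high rates of absenteeism". The Staff section says that all staff allocated to the study groups enter the quantitative part. It also reports the institutions' agreement to keep teams as stable as they can, which is a commitment to effort and not a guarantee.

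For boys and parents, Quantitative Analyses adds: "For combining the within-group pre-post comparisons and the between-group comparisons in our analyses, we will use the repeated measures ANOVA". Their two assessments are in the third week of detention and in the week of departure (Assessments).

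**The concern.** GLM repeated measures takes one row per person and one column per round, and SPSS removes any row with an empty cell. A group worker who leaves, is hired after the first round, or is absent for one round is lost entirely, including the forms that were returned. Over a year or more of quarterly rounds this adds up, and the article names turnover and absence as features of the setting.

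Three things are at stake. First, the part B test would rest on the staff who stayed and answered every time, not on all allocated staff. Second, parts A and B of the same questionnaire, completed by the same people in the same rounds, would be analysed on different sets of staff. Third, precision falls in a sample that is already small.

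**Working it through.** **Inputs from the article**
- Interval between staff rounds: 3 months (JJI Staff).
- Five groups, three FC and two UC, with about 10 group workers each (Setting): 5 × 10 = about 50, of whom 30 FC and 20 UC. Team leaders and psychologists also answer but are not counted here.
- Software: SPSS 23.

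**Inputs assumed**
- *Number of rounds K.* The only duration to lean on is for adolescents and parents, whose recruitment "will last 21 months, including the pilot stage of 7 months". Without the pilot, 21 − 7 = 14 months holds rounds at months 0, 3, 6, 9 and 12, so K = 5. With the pilot, rounds at months 0 to 21 give K = 8.
- *Yearly turnover t and non-response per round a.* The article calls turnover and absence high but gives no rates, so a range is shown.

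The article states no figure for complete staff series, so there is none to reproduce.

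**Formula.** The first and last rounds are (K − 1)/4 years apart, so the share of starters with a complete series is

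(1 − t)^((K−1)/4) × (1 − a)^K

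| t | a | K = 5 | K = 8 |
|---|---|---|---|
| 10% | 0% | 0.90 = 90%, 45 of 50 | 0.90^1.75 = 83%, about 42 of 50 |
| 20% | 5% | 0.80 × 0.95^5 = 62%, 31 of 50 | 0.80^1.75 × 0.95^8 = 45%, about 22 of 50 |
| 30% | 10% | 0.70 × 0.90^5 = 41%, about 21 of 50 | 0.70^1.75 × 0.90^8 = 23%, about 12 of 50 |

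In the last cell about 7 FC and 5 UC workers remain (30 × 0.23 and 20 × 0.23).

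**Share of returned forms used.** If each leaver is replaced at once, 50 × K × (1 − a) forms come back, and GLM uses 50 × K × the complete share. The ratio is the complete share divided by (1 − a). At t = 20%, a = 5% this is 0.62/0.95 = 65% (K = 5) or 0.45/0.95 = 47% (K = 8). At t = 30%, a = 10% it is 0.41/0.90 = 46% or 0.23/0.90 = 26%. A mixed model or GEE uses all returned forms.

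**Does the loss bias the FC-UC contrast?** A simulation took 8 rounds, person SD 1 and residual SD 1, with baseline leaving of about 25% a year and leaving that depends on the last score (log-odds 0.5 per point). It raised the completers' mean by about 0.27 points. With this selection in one arm only, a false FC-UC difference of about 0.29 appeared. With the same selection in both arms, the contrast was nearly unaffected. All these settings are assumptions, so the result shows the condition for bias and not its size in this study.

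**Boys and parents.** With two assessments, the loss in a repeated measures ANOVA equals the share without an exit assessment. Of the 160 expected, 10% missing would leave 160 × 0.90 = 144 pairs and 30% would leave 160 × 0.70 = 112. The article gives no such rate.

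**The case against.** - *The loss may be small.* No rates are given, and the institutions agreed to work for stable teams. At 10% turnover with no missed rounds, 83–90% of starters stay. This stands as the favourable end of the range. Reaching it needs almost every form returned, which sits badly with the article's own account of absenteeism.
- *The methods are provisional.* True, but the article leaves the final choice open because normality is unknown. For normally distributed data, Table 3 keeps GLM however incomplete the series are.
- *Incomplete series may be imputed under an analysis plan not shown.* This cannot be excluded, and the absence of a missing-data section is not the point. The point is that the named procedure, used as it stands, decides who is analysed.
- *GEE for part A may have nothing to do with missing data.* Part A has five-point items and part B ratings from 1 to 10, and the article ties test choice to measurement level. This is a fair explanation. The mismatch in who is analysed remains whatever the reason.
- *The wider reading for boys and parents.* A reader might infer that they lose data in the same way because stays end unexpectedly. The article says that the court's interim decision determines length of stay and that exit assessments fall in the departure week. It does not say that exits are unplanned or missed unevenly, and the researchers help with scheduling. These participants have two assessments, and their between-group tests in Table 3 are t or chi-square tests. For them the matter is secondary.

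**Conclusion.** The concern holds for part B of the staff questionnaire. The named procedure needs complete series, and the article describes a workforce in which these cannot be relied on. Under the stated assumptions (5 to 8 rounds, about 50 group workers), complete series range from 83–90% of starters in the favourable case to 23–41% at 30% yearly turnover and 10% non-response per round. Staff hired after the first round are lost as well and are not in these figures.

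The sure cost is lower precision and a result that describes only staff who stayed and always answered. A reader might infer that the FC-UC comparison is biased, or that the remaining staff are the more satisfied ones. The article does not support either: bias needs reasons for leaving or missing rounds that differ between arms, and nothing in it shows that they do. The point touches one instrument of one of eight hypotheses. The change is worth making because it is cheap.

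**What to change.** In Table 3, replace the part B entry by a linear mixed model on all returned forms:
- random intercept for person;
- fixed effects for condition, round and condition-by-round;
- team accounted for with a small-sample method: Satterthwaite or Kenward-Roger degrees of freedom, as the software allows, or team as a fixed effect within condition.

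As a secondary change, fit the pre-post analysis for boys and parents, where the text now says "we will use the repeated measures ANOVA", as a mixed model with a condition-by-time term. That term is what the two-group pre-post ANOVA tests, so it must not be left out. Participants without an exit assessment then still contribute their baseline.

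The cost is wording in Table 3 and in Quantitative Analyses, with no new data. There are limits. With five teams (three FC, two UC) the team variance is poorly estimated. If team is a fixed effect, the conclusion applies to these five teams only. The model also assumes that data are missing at random, so rounds completed and reasons for leaving should be reported by arm.
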